To further assess the impact of death (estimated at around 6% of the randomised subjects in the first 12 months after randomisation) on our potential treatment effect, a sensitivity analysis will be undertaken by excluding those subjects who have died. If there is any indication of a differential effect on deaths by treatment, models may be considered that allow the censoring to be informative. For participants that are lost to follow up at some time during the 12 month follow-up (estimated to be around 15% of those randomised), their information will be included in the statistical models up to the point that they are lost to follow up. Sensitivity analyses will be undertaken using multiple imputation (assuming data are missing at random), and, if necessary, and the data permit, specify the mechanism of missing data via a pattern mixture model assuming informative missingness.

The secondary outcomes - total number of COPD exacerbations requiring hospital admission and total number of emergency hospital admissions (all causes) - will each be analysed in the same way as for the primary outcome described above.

Disease related health status (measured using the COPD Assessment Test (CAT)), generic health-related quality of life (EQ5D-5L) and Hull Airways Reflux Questionnaire (HARQ), FEV1 and FVC are each measured at baseline, and at 6 and 12 month follow-up. A mixed effects model will be used to compare each outcome by randomisation group unadjusted and adjusted for centre, patient characteristics and/or baseline clinical variables. Mixed effects models assess rates of change with allowance for the correlation structure of the repeated measures data. Fixed effects will include assessment, treatment, centre and other relevant patient related variables and patient will be fitted as a random effect. A treatment-time interaction will be included to assess the differential treatment effect on rate of change in outcome. Alternative correlation structures will be considered and the most appropriate selected based on the log-likelihood and Akaike's Information Criterion (AIC) of the model. All randomised patients with at least one valid measurement will be included in the analysis and missing outcome data assumed to be missing at random.

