## PROPOSED ANALYSES

Predefined cutoffs will be used to risk stratify sub-study participants for occult, previously undiagnosed heart disease:

Hs TnI levels will be analysed using cutoffs that we have shown to be highly predictive in detecting subjects at high risk of silent cardiac target organ damage.

Pre-determined imaging cut-offs for in defining "occult, previously undiagnosed heart disease:

- Echo bi-plane LV EF<40% with dilated or non-dilated LV.
- Heart failure with mid-range EF (40-49%) for as per most recent ESC guidelines
- Heart failure with preserved EF ( $\geq 50\%$ ) who additionally have, as per ESC guidelines:
  - either NT-proBNP $\geq 125$  pg/ml
  - or with evidence of diastolic dysfunction (defined as abnormal LV relaxation by Doppler imaging, ie E/E' $>13$  or echo-enhanced left atrial volume $>34$  ml/m^2 or left ventricular hypertrophy diagnosed as LV mass index  $\geq 115$  g/m^2 for males and  $\geq 95$  g/m^2 for females. If current guidelines are superseded during the course of the study, the diagnostic criteria described in these will be used.

Statistical analyses will be according to the intention to treat principle. The primary outcome of number of COPD exacerbations requiring antibiotics and/or oral corticosteroids in the 12 month study period will be compared between randomised groups overall and in each subgroup (high and low risk occult heart disease) using negative binominal regression with length of time in study as an offset. To assess which biomarkers, their optimal cut-offs and/or which imaging outcome is the best method of identifying those most likely to benefit we will use ROC analysis along with sensitivity and specificity of the specific biomarker and imaging outcomes in identifying those which will show benefit. Benefit will be defined as no exacerbations during follow-up. We may

use logistic regression to assess which biomarkers/imaging measurements are best predictive alone or in combination of a beneficial outcome in terms of a reduction in COPD exacerbations.

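### The cardiac sub-study's benefit label ignores time at risk, so dying or being lost before a first exacerbation is scored as benefit

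*Protocol*

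**What the plan says.** Appendix 6, Proposed analyses, sets up two kinds of analysis. The first compares exacerbation counts between arms, overall and within high- and low-risk groups, "using negative binominal regression with length of time in study as an offset". The second looks for the markers, cut-offs and imaging measures that best identify those who will benefit, by ROC analysis with sensitivity and specificity. For the second it states: "Benefit will be defined as no exacerbations during follow-up". It adds that the team may "use logistic regression to assess which biomarkers/imaging measurements are best predictive alone or in combination" of a beneficial outcome. The section opens with "Statistical analyses will be according to the intention to treat principle". It gives no minimum follow-up for the label and no rule for death or loss.

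The second analysis serves the sub-study's secondary objective: finding the combination of markers that reliably identifies the patients who will benefit.

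Section 10.3 expects deaths, "estimated at around 6% of the randomised subjects in the first 12 months after randomisation", and loss to follow-up, "estimated to be around 15% of those randomised". Of those lost it says that "their information will be included in the statistical models up to the point that they are lost to follow up". Its sensitivity analyses (excluding deaths, multiple imputation, pattern-mixture models) are written for the main trial's count and repeated-measures models.

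**The concern.** The chance of having no exacerbation falls steadily as time at risk accumulates. A yes/no label that ignores time at risk therefore mixes two things: not exacerbating, and not being observed for long. Someone who dies in month 2 without an exacerbation meets the definition of benefit. Reading follow-up as the 12-month window does not help, because that person still has no exacerbation in the window.

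The markers are NT-proBNP, troponin, hs-CRP, galectin and echocardiographic measures. If one of them predicts death or early exit, that alone pushes it towards predicting the benefit label. Sensitivity, specificity and the chosen cut-offs would then partly describe who dies or drops out, with death counted as a success.

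**Working it through.** **Inputs.** Exacerbation rate 2.22 per year, SD 1.86 (section 10.1 and Appendix 6, Sample size); sub-study size about 900; deaths 6% and losses 15% (section 10.3). Assumed, because the protocol gives no figures: the distribution of exit times, and the exacerbation rate of those who leave early.

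**The plan's own figure.** With 900 participants, 10% stopping medication and 50% at high risk, each arm has 900 × 0.9 × 0.5 / 2 = 202.5. A difference of 0.52 with SD 1.86 at two-sided 5% gives 80.3% power, against the stated 80%. The other three rows give 80.1–80.2%. The power table reproduces and is not in dispute.

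**Chance of no exacerbation by time t (in years).** Negative binomial dispersion: k = (1.86² − 2.22) / 2.22² = 0.2515. Then P0(t) = (1 + 0.2515 × 2.22 × t)^(−1/0.2515).

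| Follow-up (months) | 1 | 2 | 3 | 6 | 9 | 12 |
|---|---|---|---|---|---|---|
| P(no exacerbation) | 83.5% | 70.2% | 59.5% | 37.6% | 24.9% | 17.1% |

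**Early leavers, averaged over uniform exit times.**
- Usual rate, exits over the whole year: 44.1%, which is 2.6 times the 17.1% for completers.
- Usual rate, exits in weeks 12–52: 33.7%, which is 2.0 times.
- Twice the usual rate, whole year: 26.9%.
- Twice the usual rate, weeks 12–52: 15.6%, slightly below completers.

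**Share of benefit labels held by early leavers.** For a fraction f leaving early with average probability P: share = f × P / [f × P + (1 − f) × 0.171].

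| | Usual rate, from day 0 | Usual rate, weeks 12–52 | Double rate, from day 0 | Double rate, weeks 12–52 |
|---|---|---|---|---|
| Deaths only, f = 6% | 14% | 11% | 9% | 5% |
| 15% with unascertained follow-up | 31% | 26% | 22% | 14% |

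In 900 participants, deaths alone would supply about 24 of 169 benefit labels at the high end and about 8 of 153 at the low end.

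**Effect on a marker (illustration with assumed exits).** Suppose 30% of marker-positive and 15% of marker-negative participants leave early, with identical exacerbation rates. With exits from day 0, P(benefit) is 0.70 × 0.171 + 0.30 × 0.441 = 25.2% against 0.85 × 0.171 + 0.15 × 0.441 = 21.2%, an odds ratio of 1.26. With exits in weeks 12–52 it is 1.16. The true odds ratio is 1.

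In the least favourable scenario for the concern (early leavers at twice the rate, weeks 12–52), full follow-up would give them P0 = 5.1%. The label then gives 16.7% against 16.9%, an odds ratio of 0.98, where full ascertainment would give 13.5% against 15.3%, an odds ratio of 0.86. The shift is in the same direction but smaller.

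**The case against.** Four points can fairly be made against this.

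1. **The text does not say outright that deaths count as successes.** The protocol often uses follow-up for a fixed 12 months, and section 7.12 ends clinical follow-up at the 12-month visit. Incomplete cases might be meant to stay unclassified, with the detail left to the SAP. This is arguable for losses. It does not rescue the label for deaths, because the definition as worded is met by anyone who dies exacerbation-free and the analysis is by intention to treat.

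2. **Lost does not mean unascertained.** Section 7.6 plans post-study examination of hospital and GP records and attempts GP checks for non-attenders. Section 7.10 asks those withdrawing to allow use of routine records. This stands. Retrieval would shrink the 15% component, though it is only attempted and cannot extend follow-up for those who died.

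3. **The larger shares need generous assumptions.** A reader might add 6% and 15% and infer that 34–41% of benefit labels come from early leavers. The documents do not support that: the two figures may overlap, records may be retrieved, and the baseline sample or echocardiogram is allowed up to 12 weeks after randomisation, so many of the earliest leavers have no marker. Section 10.3 also implies that early withdrawers exacerbate more. The deaths-only range is the firmer figure.

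4. **The reach is limited, and no association between these markers and exit is given.** Both are true. The bias is conditional on such an association, and the logistic model is optional.

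**Conclusion.** The concern stands for the sub-study's marker-selection analysis. The definition in Appendix 6 is a stated rule that misclassifies deaths, and losses without retrieved records, before a first exacerbation. The remedies in section 10.3 are not written for this label.

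Deaths alone supply about 5–14% of benefit labels. If all of the expected 15% loss stayed unascertained, its share would be about 14–31%, and record checks would lower it. The low ends assume exits in weeks 12–52 at twice the usual exacerbation rate; the high ends assume exits from day 0 at the usual rate. All figures rest on negative binomial counts with mean 2.22 and SD 1.86, on uniform exit times, and on the main trial's 6% and 15% holding in the sub-study.

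A reader might infer that the sub-study's main answer, or the trial's, is compromised. It is not: the negative binomial comparisons overall and by risk group carry a time offset, and the power table does not depend on the label. What is affected is the secondary objective and any logistic model using the same label. This should be corrected, but it does not threaten the trial's main conclusions.

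**What to change.** In Appendix 6, Proposed analyses, and correspondingly in the SAP:

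- Base the marker analyses on the exacerbation count with log follow-up time as offset, using the negative binomial model the section already names.
- Sensitivity, specificity and cut-offs still need a yes/no label. Define it as no exacerbation over 12 months of ascertained follow-up, from participant report or GP record.
- Do not count death or incomplete follow-up before a first exacerbation as benefit. Handle these cases by a pre-specified method, for example censoring-weighted or time-dependent ROC.
- Repeat with an alternative classification of deaths as a sensitivity analysis, since more than one choice is defensible.

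The cost is a few sentences and a little more analysis work. No new data are needed.

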## **APPENDIX 7: Contingency arrangements for COVID-19 (March 2020)**

These arrangements are put in place to minimise the risk to participants during the COVID-19 pandemic. These contingency arrangements will remain in force until advised by the Sponsor, at which point we will revert to the main study protocol.

Face-to-face contact with study participants for study purposes should cease (as described below). This change does not increase the risks for participants within BICS. There are currently no other changes to other processes within the study.

### **Study participants who are in titration**

Assessment of symptoms and participant preference should be made using a telephone assessment with a decision to fix on the current tolerated dose or the previously tolerated dose. There should be no up-titration in these situations unless the participant has previously tolerated a higher dose (and has down titrated due to an exacerbation of their COPD).

If a participant has a home blood pressure monitoring system, data from this can also be collected during the telephone assessment (along with symptoms and patient preference) and used in decision making. If information on heart rate and blood pressure is available and heart rate is 60 bpm or more and systolic BP 100mmHg or more, up-titration can be carried out. If this is done, the participant must be followed up with further telephone contact approximately one week later to confirm tolerance of the dose.

Guidance on the titration of individual participants can be sought from the CI via the trial office team.

During this period, study participants may not titrate to their maximum tolerated dose. They will not be asked to up-titrate at a later date. We will keep records of the participants affected and consider whether additional statistical analysis should be undertaken, for example a sensitivity analysis excluding the affected participants – if so, this will be reflected in the Statistical Analysis Plan.

### **Six and twelve month follow-up**

Follow-up will be by telephone rather than face-to-face.

## APPENDIX 8: Contingency arrangements for COVID-19 (restart of recruitment)

We are proposing three main changes to the protocol to allow recruitment to restart.

### 1. Reducing the number of face-to-face visits

We are reducing the number of face-to-face visits to one (recruitment), with other visits carried out by telephone or video call. If sites wish, the recruitment visit can also be done by telephone or video call. Video calls should be done using technologies approved for use in the local area by the NHS. [amendments to section 4, 7.2, 7.2.2, 7.6, 9.6.1.

PIC activity (with face-to-face recruitment) will only be used within the study at times when there are no local travel restrictions in place. At other times, PIC activity will only be used where recruitment and consent is done without a face-to-face visit (see section 7.2 (B)). [amendment to section 7.1]

### 2. Amending the inclusion criteria

We are amending the inclusion criteria. Firstly, we are amending the exacerbation criteria to: A history of at least two exacerbations requiring treatment with antibiotics and/or oral corticosteroid use in the previous year, based on patient report **OR A history of at least two exacerbations within 12 months of each other requiring treatment with antibiotics and/or oral corticosteroid since March 2019.**

Secondly, we are removing the requirement for spirometry at recruitment. The inclusion criteria will be based on an established predominant diagnosis of COPD, based on historic  $FEV_1/FVC < 0.7$  and  $FEV_1 < 80\%$  predicted. [amendments to section 6.1, 7.1.2]

*Justification for this change:*

*There is anecdotal evidence that shielding has reduced the number of exacerbations experienced by people with COPD. The ECLIPSE study has demonstrated that the frequent exacerbator phenotype is stable for at least 3 years. The modification of the inclusion criteria to include  $\geq 2$  exacerbations in any 12 month period since March 2019 enables the identification of the people at high risk of exacerbation during the time of reduced exacerbation risk during lockdown by combining exacerbations before and after the lockdown.*

*Spirometry is an aerosol generating procedure and therefore is currently not being done within the NHS unless in exceptional circumstances, with the highest levels of PPE. The use of current or historical evidence of  $FEV_1/FVC < 0.7$  has previously been permitted within the inclusion criteria within the study protocol. Previously,  $FEV_1 < 80\%$  predicted was required to be demonstrated at baseline. Going forward during the COVID-19 pandemic, historical evidence will be used for both  $FEV_1 < 80\%$  predicted and  $FEV_1/FVC < 0.7$ .*

### 3. Amending the titration schedule

We are amending the titration schedule to remove the criteria based on  $FEV_1$ . Instead, participants will be asked about changes in breathlessness since recruitment to the study – and dose will be reduced if breathlessness has worsened [section Figure 1, 8.7.1, 8.7.2].

*Justification for this change:*

*The original BICS protocol requires the dose of study medication be increased over a period of 4-7 weeks to a maximum of 5mg bisoprolol (placebo equivalent 4 tablets). Decisions to increase, fix or reduce the dose of study drug at each dose titration visit are determined by the presence of intolerable side effects (e.g. fatigue), pulse rate, systolic blood pressure and lung function ( $FEV_1$ ). To aid decision making an online algorithm has been developed that uses these data to recommend dosing decisions.*

*It will be possible to determine the presence of intolerable symptoms during a phone/video dose titration 'visit' and the provision of a digital sphygmomanometer to each participant will enable the measurement of pulse rate and systolic blood pressure. We have investigated the feasibility of participants performing spirometry during the phone/video call dose titration 'visits' but have concluded that this is not a viable option, principally because participant technique is likely to be suboptimal and the need to calibrate the equipment before use (spirometer calibration syringes are prohibitively expensive - £300 each).*

*Digital sphygmomanometers can be purchased for between £30 and £40, and we will use savings on travel expenses to purchase these.*

*As outlined previously in the protocol, the use of cardio-selective betablockers such as bisoprolol in people with COPD is safe. A systematic review of RCTs studying effects of cardio-selective blockers on lung function and respiratory symptoms in people with COPD demonstrated that the acute and chronic use of cardio-selective betablockers does not significantly reduce lung function, increase respiratory symptoms or reduce response to inhaled beta2 agonists. Moreover, since BICS started recruitment, a placebo controlled randomised clinical trial (BLOCK COPD) has reported that a year's treatment with the cardio-selective betablocker metoprolol (n=268) had no effect on lung function (FEV1) when compared with placebo (n=264). We have reviewed the dose titration data for BICS (maintaining the study blind): of the 429 participants recruited before recruitment was suspended, 49 had their dose of study medication reduced during dose titration because of a reduction in lung function (FEV1), with no significant difference between the two randomised study groups (9% vs 13%). In addition, for those who had the dose of study drug reduced during dose titration because of a reduction in FEV1, there was no difference in the absolute or relative reduction in FEV1 between the two randomised groups and only two of the 49 participants complained of intolerable breathlessness. It would appear that reductions in FEV1 during dose titration in BICS appear to be similar in magnitude and frequency between bisoprolol and placebo groups and do not manifest as increased symptoms.*

*It is therefore proposed, during phone/video dose titration, that the measurement of lung function be replaced by asking the participant whether their breathing has deteriorated since starting/ increasing study medication and that the online dosing algorithm be changed to include the answer to this question rather than changes in FEV1. If the study team have concerns about potential side effects in a participant during titration (or later on in follow-up), the participant can be seen at a face-to-face visit with appropriate COVID-19 measures in place. We note that national heart failure guidelines do not recommend spirometry during the dose titration of betablockers in people with heart failure (many of whom have COPD). The current dose titration algorithm for BICS is not routine clinical practice for people with heart failure and COPD and the measurement of lung function was included in the current protocol with the deliberate intent of being conservative. The proposed use of the symptom of increased breathlessness is more in keeping with routine clinical practice and will improve the generalisability of the study findings.*

In addition, we are proposing the following:

**4. Participants recruited at sites offering the cardiac sub-study** and who agree to take part in the cardiac sub-study will be asked to participate in an additional two face-to-face visits. The echocardiography and blood samples (soon after recruitment) and blood samples (around the 12 month follow-up) will require an additional two face-to-face visits for participants. Appropriate COVID-19 precautions will be taken (PPE, social distancing, hand hygiene).

[figure not shown]
